#### Analysis of secondary outcomes

Use of the four services within the 1-week follow-up period will be analysed using the same approach as used for the primary outcome. Help-seeking intentions, which are measured on a 7-point Likert scale, will be measured using ordinal logistic regression. In the case that some levels on this 7-point scale are underrepresented, we will consider combining adjacent categories as appropriate.

We will analyse respondents’ choices made within the DCE by estimating the conditional logit models [31] and mixed logit models [32]. These analyses will be performed using STATA (version 18). These models can be interpreted via the Random Utility Theory which assumes that individuals will choose the alternative that provides them with the highest utility. We will also estimate the Willingness to Pay (WTP), which is the dollar amount individuals are willing to pay for service changes. Relative importance of attributes will also be assessed to understand the relative impact that an attribute has on choice. For example, the preference analysis results will allow us to explore whether men prefer one service type (e.g. peer support) over another (e.g. seeing a psychiatrist). The WTP results will indicate the dollar amount men are willing to pay to receive one service compared to another (e.g. they might be willing to pay $50 more to receive services individually rather than in a group setting). The relative importance results will allow us to understand the ranking of the suicide prevention attributes (e.g. the most important factor affecting choice may be service type, followed by waiting time, cost, etc.). To explore observed heterogeneity, sub-group analyses will be undertaken by interacting the preference weights with a range of socio-demographic characteristics including age, educational attainment, employment status, income levels, etc. This will allow us to understand why individuals in one sub-group (e.g. higher educational attainment) may have different preferences compared to those in another sub-group (e.g. lower educational attainment).

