##### Service preferences

Preferences for suicide prevention services will be elicited through a DCE [16, 17]. DCEs are a survey-based method used to understand how people make choices among different service options with varying attributes. DCEs create hypothetical choice situations, where each choice (service or product) is described by a set of attributes (characteristics) and levels. The DCE will allow inferences to be drawn about the relative importance of suicide prevention service attributes by observing the trade-offs that respondents make when choosing their preferred service.

A list of seven service attributes, each with varying levels, has been constructed based on a literature review and refined through interviews with men with lived experience of suicidal thoughts (*n* = 7). The final list of attributes is out-of-pocket cost, service type (i.e. self-help resources, peer support, counselling, healthcare), service mode (i.e. online, phone, face-to-face), waiting time, availability, service environment (i.e. individual or group), and service linkage (i.e. linking to services helping with employment, finances, housing, relationships). Attribute levels will be altered across the scenarios presented and respondents will be asked to choose their preferred hypothetical suicide prevention service. Each scenario will include two suicide prevention services constructed using the seven attributes and an additional option to choose neither. Scenarios will be presented to participants in the format shown in Fig. 3.

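### DCE sub-group interactions on raw logit weights mix preference with choice consistency, so they should not on their own be read as preference differences

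*Protocol article*

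**What the plan says.** The Service preferences section describes the choice task: "Each scenario will include two suicide prevention services constructed using the seven attributes and an additional option to choose neither".

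Under Analysis of secondary outcomes, conditional and mixed logit models are planned for the choices, with this reading: "These models can be interpreted via the Random Utility Theory which assumes that individuals will choose the alternative that provides them with the highest utility". WTP is also planned: "We will also estimate the Willingness to Pay (WTP), which is the dollar amount individuals are willing to pay for service changes". So is the relative importance of attributes.

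Sub-groups come last: "sub-group analyses will be undertaken by interacting the preference weights with a range of socio-demographic characteristics including age, educational attainment, employment status, income levels". The intended reading follows directly: "This will allow us to understand why individuals in one sub-group (e.g. higher educational attainment) may have different preferences".

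No scale term is mentioned. WTP is not named as the quantity to be compared between sub-groups; the comparison is stated on the preference weights.

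**The concern.** The question is whether sub-groups want different things, that is, whether they trade the attributes off in different proportions. The stated method compares raw logit weights. In a random-utility logit those weights are identified only up to a scale that is inversely related to the spread of the error term. If one sub-group answers a seven-attribute task more noisily, all its weights shrink towards zero together. Every interaction with a non-zero weight is then non-zero, although the trade-offs are the same.

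Mixed logit does not remove this in principle: interactions on the coefficient means still carry any group difference in scale.

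At stake is the reading of the sub-group results. Lower consistency among less-educated men, for example, could be reported as weaker preferences across the board.

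**Working it through.** **Inputs from the document.** 380 men (Sample and recruitment); seven attributes; two services plus a neither option, so three alternatives per scenario (Service preferences); conditional logit with weights interacted by sub-group (Analysis of secondary outcomes). The document gives no figure for the sub-group analysis, so there is none to reproduce.

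**Assumed inputs.** 8 scenarios per man, 11 coefficients, two equal sub-groups, the true weights, and the ratio of the two groups' scales. None of these is in the document.

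**Step 1: what the interaction estimates.** In sub-group g the estimated weight is λ_g × β_g, where β_g is the preference and λ_g the scale. The interaction is therefore λ₁β₁ − λ₀β₀. With identical preferences (β₁ = β₀ = β) it equals (λ₁ − λ₀)β, which is zero for a non-zero β only if the scales are equal.

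**Step 2: illustration.** Take an assumed cost weight of −0.8, an assumed weight of 0.4 for service environment, and λ₁/λ₀ = 0.7.
- Weights in the noisier group: 0.7 × (−0.8) = −0.56 for cost and 0.7 × 0.4 = 0.28 for environment.
- Interactions: −0.56 − (−0.8) = 0.24 and 0.28 − 0.4 = −0.12, although preferences are identical.
- WTP in cost units: 0.4/0.8 = 0.5 in one group and 0.28/0.56 = 0.5 in the other. The scale cancels.

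**Step 3: how often a test would reject.** Two separately programmed simulations gave both groups the same β. Simulation A used a joint Wald test on 11 degrees of freedom with 150 replicates. Simulation B used a joint likelihood-ratio test on 11 degrees of freedom with 400 replicates (200 at ratio 0.9). Rejection rates at nominal 5%:

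| Scale ratio | A: joint interaction test | B: joint interaction test |
|---|---|---|
| 1.0 | 3% | 6% |
| 0.9 | not run | 12.5% |
| 0.8 | 24% | 37% |
| 0.7 | 63% | 78% |
| 0.5 | 99% | about 100% |

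Monte Carlo standard errors are √(p(1−p)/R): for example √(0.24 × 0.76/150) = 3.5 points for A at 0.8, and √(0.125 × 0.875/200) = 2.3 points for B at 0.9.

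**Step 4: the scale-free alternatives on the same data.** A test of common preferences with a free relative scale (10 degrees of freedom) rejected in 3–5% in A and 5–7% in B. Between-group WTP comparisons rejected in 1–3% in A (joint test of ten ratios) and 3–7% in B (one attribute). In A, an unequal 30/70 split gave the same pattern: at ratio 0.8 the joint interaction test rejected in 29%, the free-scale test in 7% and the WTP test in 5%.

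**The case against.** The strongest reply is that the document states no formal test: no null hypothesis, significance level or decision rule. The aim is exploratory and the wording cautious, since sub-groups may differ. This is also a condensed article, and a scale term or a ratio-based report could stand in a fuller plan. Against that, the article does fix both the method and the reading given to it, and the reading does not follow from the method. The point is therefore not only an omission.

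A second reply is that an interacted model is the ordinary route to sub-group weights and hence to sub-group WTP, which is already planned. This stands. The interacted model need not be replaced; only the quantity that is interpreted needs to be named.

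Third, the size rests on assumptions. Nothing in the document shows that consistency differs by education or any other characteristic, and at a ratio of 0.9 the inflation is modest. The gap between 24% and 37% at 0.8 shows how much the assumed inputs matter. Mixed logit was not simulated, so no rate can be given for it. All of this stands.

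Fourth, WTP has its own weakness: it moves when only the cost weight differs. With an environment weight of 0.4 in both groups and cost weights of −0.8 and −0.6, WTP is 0.5 and 0.4/0.6 = 0.67. This matters for the income and employment sub-groups. The power of either alternative was not assessed.

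A reader might infer that sub-groups will be falsely declared different, that the secondary aim fails, or that services would be targeted on an artefact. The document supports none of these. It has no declaration rule, the pooled weights and WTP answer the aim of learning what these men value, and it proposes no targeting by education or employment.

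**Conclusion.** The concern holds as a caution about interpretation. Interactions on raw logit weights combine preference and choice consistency, yet the article reads them as preference alone. That follows from the algebra and needs no assumption about effect size.

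How much it matters here is unknown. In the simulated setting the inflation is absent at equal scale, modest at a ratio of 0.9 and large at 0.7 or below. Those rates depend on the assumed number of scenarios, coefficients, weights and scale ratios, and apply to conditional logit only.

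The effect is confined to an exploratory breakdown of a secondary outcome. The primary click-through result and the pooled DCE estimates are untouched. It is worth correcting because the correction is cheap.

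**What to change.** Keep the interacted model and add to Analysis of secondary outcomes a statement along these lines:

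> Sub-group differences in preferences will be judged on scale-free quantities: between-group differences in WTP with 95% confidence intervals, or a likelihood-ratio test of common preferences with a group-specific scale parameter against the fully interacted model. Raw interaction coefficients alone will not be interpreted as differences in preference.

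Add a note that WTP also moves when only the cost weight differs, so that WTP contrasts by income and employment need care; the likelihood-ratio test with a free scale is a useful companion there.

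No new data or procedures are needed. The price is slightly more analysis work and some loss of precision: ratio comparisons tend to have wider intervals, and the free-scale test has one fewer degree of freedom (10 instead of 11 in the simulated model). The loss of precision has not been quantified.

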#### Exploratory analyses

We will also perform exploratory analyses to assess the potential moderating effects of demographic and clinical variables collected, such as participant age and the severity of their suicidal ideation, as well as the length of time participants spent viewing the video message. These analyses will be performed by entering interaction terms into the abovementioned models. Moderators will be assessed one at a time and using separate models.

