### Outcome measures

The full schedule of assessments is shown in Table 1.

**Table 1 Tab1:** Summary of the primary, secondary, other outcome measures, and data collection time points

Outcome measures	Assessment	Baseline	Post-intervention	One-week follow-up
*Primary outcome*				
Help-seeking behaviour	Click-throughs	–	✓	–
*Secondary outcomes*				
Use of support services	Self-report item	–	–	✓
Help-seeking intentions	Self-report item	–	–	✓
Service preferences	Discrete Choice Experiment	–	✓	–
*Exploratory outcomes*				
Awareness of services	Self-report item	–	✓	–
Frequency of services chosen	Click-throughs	–	✓	–
Intervention acceptability	Theoretical Framework of Acceptability Questionnaire	–	✓	–
Time spent viewing video	Seconds of video play	–	✓^a^	–
Suicidal distress	University of Washington Risk Assessment Protocol	✓	✓	–
Demographics	Self-report item	✓	–	–
Suicidal thoughts	Suicidal Ideation Attributes Scale	–	✓	–
General mental wellbeing	Short Warwick Edinburgh Mental Wellbeing Scale	–	✓	–
Psychological distress	Kessler Psychological Distress Scale	–	✓	–
Loneliness	Three-Item Loneliness Scale	–	✓	–
Anhedonia	Snaith-Hamilton Pleasure Scale	–	✓	–
Physical and mental health	Self-report item	–	✓	–
Barriers to services	Barriers to Access to Care Evaluation Scale	–	–	✓
*Process outcomes*				
Service engagement patterns	Service usage data provided by four support services	–	–	✓

^a^Measured during intervention delivery

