#### Exploratory outcomes

A range of exploratory measures will be used to assess aspects of service awareness and use, as well as key demographic and clinical moderating variables.

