##### Time spent viewing the video

Participants can start, stop, and skip the video message at any time. We will capture the total number of seconds of the video that participants viewed.

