##### Severity of suicidal ideation and past attempts

The Suicidal Ideation Attributes Scale (SIDAS) [24] will be used to measure the severity of suicidal thoughts in the past month. This will be assessed at the post-intervention assessment. The SIDAS consists of five items that assess the frequency of suicidal thoughts, the controllability of suicidal thoughts, the closeness an individual has come to making a suicide attempt, the level of distress associated with the thoughts, and the impact of these thoughts on daily functioning. Each item is rated on an 11-point scale (0–10). Item two (controllability) is reverse scored. Total scores on the SIDAS range from 0 to 50, with higher scores indicating more severe suicidal ideation. Previous suicide attempts and self-injury will also be assessed using two questions that ask participants to indicate whether they have attempted suicide (a) in their lifetime and (b) in the past 30 days. Participants respond on a 3-point Likert scale: 0 (‘No, never’), 1 (‘Yes, once’), and 2 (‘Yes, more than once’). Participants are also asked to report the date of their most recent attempt.

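### Two planned moderators are measured after randomisation: viewing time should not be tested as a moderator, and ideation severity (SIDAS) only descriptively

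*Protocol article*

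**What the plan says.** The Exploratory analyses section of the protocol article plans to examine possible moderation by demographic and clinical variables, with age and ideation severity as the examples, "as well as the length of time participants spent viewing the video message". The method is stated: "These analyses will be performed by entering interaction terms into the abovementioned models". Each moderator gets its own model.

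The timing of the named moderators is given elsewhere:

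- **Viewing time.** The Table 1 footnote reads "Measured during intervention delivery". The section on time spent viewing adds: "Participants can start, stop, and skip the video message at any time".
- **Ideation severity (SIDAS).** Its section says "This will be assessed at the post-intervention assessment", and Table 1 has no baseline tick. The scale "will be used to measure the severity of suicidal thoughts in the past month".
- **Age.** The Demographics section places it at baseline.

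The introduction to Exploratory outcomes says the measures cover service awareness and use, "as well as key demographic and clinical moderating variables". It does not list which measures are meant as moderators.

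**The concern.** A moderator test asks whether the effect of arm differs between kinds of participant. Randomisation supports this when the participant's kind is fixed before allocation: within each level of the variable, the arms are still comparable. If the arm can change the variable, that protection is lost. A man who watches a self-reliance message to the end and a man who watches suicide statistics to the end may differ in motivation, and a difference in their click rates mixes that selection with any effect of the message.

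At stake is the reading of the exploratory results. A finding that the target messages work in men who watch them through could appear with no video effect at all. Because the plan affirmatively specifies this analysis, following it as written leads there.

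**Working it through.** **Step 1: timing.** The Assessment schedule section gives the order as baseline questionnaires, then video, then post-intervention questionnaires. Set against the planned moderators and other candidates:

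| Variable | When measured | Can the assigned video change it? |
|---|---|---|
| Age, other demographics | Baseline | No |
| UWRAP stress, baseline value | Baseline | No |
| Viewing time | During the video | Yes, directly |
| SIDAS | Post-intervention only | Only how it is reported (past-month recall) |
| Well-being, distress, loneliness, anhedonia | Post-intervention only | Mainly how they are reported, if used as moderators at all |

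Two of the three moderators named in the Exploratory analyses section are therefore post-randomisation.

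**Step 2: what a null trial can show for viewing time.** The plan has no figure of its own to reproduce here, so this is an illustration with assumed inputs. Half of the men in every arm are motivated and click with probability 0.40; the other half click with probability 0.10. Neither the arm nor viewing affects clicking. Let *a* be the share of motivated men who watch to the end and 1 − *a* the share of unmotivated men who do. Half of each arm then watches fully, and a fraction *a* of full viewers is motivated:

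- P(click | full) = 0.40*a* + 0.10(1 − *a*)
- P(click | part) = 0.40(1 − *a*) + 0.10*a*

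Target arms, *a* = 0.8: full 0.32 + 0.02 = 0.34; part 0.08 + 0.08 = 0.16. The overall rate is 0.5 × 0.34 + 0.5 × 0.16 = 0.25. In every control scenario below it is also 0.25, so there is no effect of arm.

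For control *a* = 0.5, both control rates are 0.25. The odds ratio in full viewers is (0.34/0.66)/(0.25/0.75) = 1.55, and in part viewers (0.16/0.84)/(0.25/0.75) = 0.57. Their ratio is 2.70. Changing only the control arms:

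| Control completion, motivated/unmotivated | Control click, full | Control click, part | OR, full viewers | OR, part viewers | False interaction ratio |
|---|---|---|---|---|---|
| 50/50 | 0.25 | 0.25 | 1.55 | 0.57 | 2.70 |
| 60/40 | 0.28 | 0.22 | 1.32 | 0.68 | 1.96 |
| 70/30 | 0.31 | 0.19 | 1.15 | 0.81 | 1.41 |
| 80/20 | 0.34 | 0.16 | 1.00 | 1.00 | 1.00 |

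Half of the men complete the video in every arm and every row. Equal completion rates by arm would therefore not reveal the problem.

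**Step 3: simulation of the interaction test.** Logistic models were fitted with 228 target men (3 × 76) and 152 control men (2 × 76), 2,000 runs per setting. Clicking depended on arm (log-odds ratio 0.9, the same for all men) and on latent motivation. With a moderator unaffected by arm, the interaction test rejected in 4.5% of runs, close to nominal. When the target videos raised the moderator and strengthened its link with motivation (extra loading 0.3, 0.6, 1.0), rejection rose to 8.6%, 12.5% and 15.6%, with median false coefficients of 0.17, 0.27 and 0.34. These parameters are also assumed.

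**Step 4: SIDAS.** A video of about two minutes cannot alter past-month ideation, only the answers about it. A shift in reporting common to all arms would not make the arms differ; the shift would have to differ between videos. No figure in the document bears on its size, so none is computed.

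**The case against.** The strongest reply is that these analyses are labelled exploratory, that the short baseline is deliberate (to limit pre-exposure, as explained under the assessment schedule), and that control and target videos share length, style and actor, so viewing behaviour and reporting may differ little between arms. Much of this stands. The label limits the consequence, and matched formats make the 2.7 case only one end of a range that reaches 1.0. But neither the label nor the reason for the timing makes viewing time a pre-randomisation trait, and the messages differ by design.

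Several stronger readings are tempting, and the document does not support them:

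- *All the planned moderators are invalid.* Age and the other demographics are collected at baseline.
- *Well-being, distress, loneliness and anhedonia are declared moderators.* Only age, ideation severity and viewing time are named; the introduction to Exploratory outcomes speaks of moderating variables in general.
- *The scales are shown to follow the service links.* Table 1 gives no order within the post-intervention step. That order is plausible from the trial design text but is not stated.
- *SIDAS is as compromised as viewing time.* Its past-month recall argues against that. Well-being and distress also have fixed recall windows (two and four weeks); no window is stated for the loneliness scale, so the reassurance is weaker there.
- *A false moderator result would steer a planned campaign.* The Objectives section says only that the findings may underpin one, and does not tie it to the moderator tests.

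**Conclusion.** The point holds, with different force for the two variables. Viewing time is a clear error: it is a response to the assigned video, and its interaction with arm does not estimate moderation. The false interaction ranges from 2.7 to none in the illustration, depending on how differently completion tracks motivation in target and control arms. The document gives no data on this, so the direction and size in this trial are unknown. For SIDAS, and any other post-video scale used as a moderator, the risk is smaller and depends on differential reporting, which is possible but not shown. The primary and secondary comparisons between arms are unaffected.

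**What to change.** Amend the Exploratory analyses section as follows:

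1. Limit moderation tests to pre-video variables (age and the other baseline demographics, baseline UWRAP stress) and to history the video cannot change (lifetime attempts, prior diagnosis).
2. Remove viewing time as a moderator. Report it as an outcome by arm, and describe any link with clicks as a post-randomisation association.
3. Report interactions with SIDAS and other post-video scales as descriptive only, after showing their distributions by arm. Similar distributions are reassuring but not proof, as Step 2 shows.

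Using random arm as an instrument for viewing time is not a way round this. The arms differ in message content and can affect clicks other than through seconds watched.

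The change is to wording only and needs no new data. The cost is that fewer clinical moderators can be claimed.
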